### Sample size calculation

Count data of the parallel controlled trial (1:1) will be analyzed statistically using a two-sided superiority test where α = 0.05, power = 90 %. The formula used for calculation is as follows:$$ n=\frac{{\left({Z}_{1-a}+{Z}_{1-\upbeta}\right)}^2\times \left({\sigma}_1^2+{\sigma}_2^2\right)}{\delta^2} $$

It is assumed that the change in the standard deviation of the Sunnybrook facial grading system score before and after the treatment in the control group is 10 points and that that in the treatment group is 18 points. A change will be considered clinically significant if the change of Sunnybrook scale score before and after the treatment in the treatment group is 13 points higher than that in the control group. The estimated sample size is arrived at as follows:$$ n=\frac{{\left({Z}_{1-a}+{Z}_{1-\upbeta}\right)}^2\times \left({\sigma}_1^2+{\sigma}_2^2\right)}{\delta^2}=\frac{{\left(1.96+1.28\right)}^2\times \left({10}^2+{18}^2\right)}{13^2}\approx 26.33 $$

It is assumed that the change in the standard deviation of HB scale score before and after the treatment in the control group is 1 point and that that in the treatment group is 3 points. A change will be considered clinically significant if the change of HB scale score before and after the treatment in the treatment group is 2 points higher than that in the control group. The estimated sample size is arrived at as follows:$$ n=\frac{{\left({Z}_{1-a}+{Z}_{1-\upbeta}\right)}^2\times \left({\sigma}_1^2+{\sigma}_2^2\right)}{\delta^2}=\frac{{\left(1.96+1.28\right)}^2\times \left({1}^2+{3}^2\right)}{2^2}=26 $$

It is determined that there should be at least 27 patients in each group. The dropout rate is considered to be 20 %, and thus at least 33 patients should be enrolled in each group. Hence, a total of 132 patients are required to conduct this study.

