### Interventions

#### Acupuncture therapy

Acupuncture will be performed by specialists in traditional Chinese medicine, and the protocol will follow the details of the Standards for Reporting Interventions in Clinical Trials for Acupuncture 2010 checklist [22, 23], as shown in Table 1.

**Table 1 Tab1:** Details of acupuncture intervention

		Description
Acupuncture rationale	Style of acupuncture	Traditional Chinese medicine
	Rationale for treatment	Acupuncture has been historically used to treat facial palsy. Additionally, it is known to be a safe treatment used in a wide range of symptoms caused by Bell’s palsy
	Extent to which treatment varied	The subjects of the intervention group all receive the same acupuncture or electroacupuncture treatment
Details of needling	Number of needle insertions per subject per session	10
	Names of the insertion points (uni- or bilateral)	GB14, TE23, Qianzheng, LI20, SI18, ST4 (unilateral, affected side), LI4, LR3 (bilateral)
	Depth of insertion	10–30 mm (exact depth shown in Table 2)
	Response sought	*Deqi*
	Needle stimulation	Some in electric stimulation, others in manual stimulation (exact details are in the text)
	Needle retention time	20 minutes
	Needle type	0.30 mm (diameter) × 25 mm (length) disposal needle (Huatuo Acupuncture, Suzhou, China)
Treatment regimen	Number of treatment sessions	12
	Frequency and duration of treatment sessions	3 sessions/wk for 4 wk
Other components of treatment	Details of other interventions administered to the acupuncture group	No other interventions
	Setting and context of treatment	All subjects are informed that they will receive acupuncture or electroacupuncture treatment, which can potentially reduce Bell’s palsy symptoms; however, the non-acupuncture control group would have to complete the evaluations during the first week before receiving the same treatment as the acupuncture group.
Practitioner background	Description of participating acupuncturists	Specialists in traditional Chinese medicine with at least 3 years of practice in acupuncture
Control or comparator interventions	Rationale for the control or comparator in the context of the research question	Non-acupuncture control is used as a control because sham acupuncture cannot be a substituted for a physiologically inert placebo, and Western medicine is recommended in the guideline.

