### Stable and recovery stages

Patients in groups A–C will receive straight or oblique acupuncture with a depth of 10–30 mm at the Cuanzhu (BL2), Yangbai (GB14), Sizhukong (TE23), Qianzheng, Yingxiang (LI20), Quanliao (SI18), Dicang (ST4), Hegu (LI4), and Taichong (LR3) points (identified according to the method of point location issued by the WHO) to bring out the desired sensation of *deqi* from the eighth day after palsy onset. The needles will be retained for 20 minutes. The electroacupuncture will be performed once every 2 days. Accordingly, patients in groups A–C will receive electroacupuncture therapy at the Yangbai (GB14)-Sizhukong (TE23), Quanliao (SI18)-Yingxiang (LI20), and Qianzheng-Dicang (ST4) points (2 Hz, density wave, 20 minutes). All patients will be given therapies until the endpoint of complete recovery or study withdrawal.

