### Primary outcome

Evaluation will be performed using facial paralysis evaluation scale (HB and Sunnybrook scales). Measurements will be performed at the above-mentioned time points and at the first month after therapy by three physicians, and the averaged value will be recorded. Meanwhile, the time for the first change in the score after the start of treatment will be labeled. The period from palsy onset to the first change in the facial paralysis evaluation scale score and the patient’s overall recovery period will be recorded, and comparison between the interventional groups and the control group will be conducted.

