### Statistical analysis

In this study, statistical analyses of data will be performed by professionals rather than investigators using intention-to-treat and per-protocol approaches. All demographic and clinical characteristics of the subjects (such as sex, age) will be processed based on descriptive analyses. Quantitative data will be presented as average, standard deviation, median value, and range. Qualitative data will be presented as the frequency and percentage.

For the primary outcome measurements, a repeated-measures multifactorial analysis will be performed to identify differences between groups (differences within each group based on time, and the effects of the interaction of the variables based on group) to compare the differences in HB and Sunnybrook score changes between the interventional and control groups based on time (baseline, every treatment time and 1 month after palsy onset). The period from the onset to the first change in facial paralysis evaluation scale score in and the patients’ overall recovery period will be compared using one-way analysis of variance (ANOVA) between all groups. For the secondary outcome measurements, a χ^2^ test will be used to compare the edema onset frequency of the facial nerve on the affected side. One-way ANOVA will be applied to identify differences in results of facial nerve electromyography and F-wave detection between groups. In cases of non-normally distributed data, the Kruskal-Wallis H test will be performed.

All adverse events reported during the study will be included in the clinical report, and the prevalence of adverse events will then be calculated. The percentage of participants with adverse events in each group will be calculated and compared using the χ^2^ test or Fisher’s exact test. Statistical analyses will be performed using IBM SPSS for Windows version 19.0 statistical software (IBM, Armonk, NY, USA). All the tests will be two-sided, and a *P* value <0.05 will be considered statistically significant.

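### One-way ANOVA is fixed for time to first score change and time to recovery, although patients who withdraw or stay unrecovered have no such time

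*Protocol article*

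**What the plan says.** The Primary outcome section lists two durations beside the House-Brackmann and Sunnybrook scores. One is "The period from palsy onset to the first change in the facial paralysis evaluation scale score". The other is the patient's overall time to recovery: "overall recovery period will be recorded, and comparison between the interventional groups and the control group will be conducted".

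The Statistical analysis section fixes the test for both: the "overall recovery period will be compared using one-way analysis of variance (ANOVA) between all groups". The only alternative is for skewed data: "In cases of non-normally distributed data, the Kruskal-Wallis H test will be performed". The same section promises intention-to-treat and per-protocol analyses.

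Elsewhere the article expects patients who will not have these times:

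- Stable and recovery stages: "All patients will be given therapies until the endpoint of complete recovery or study withdrawal".
- Sample size calculation: "The dropout rate is considered to be" 20%.
- Discussion: whether recovery will be complete is named as part of the study's greatest uncertainty.

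The length of observation is given in different ways. Table 1 has "3 sessions/wk for 4 wk". The Abstract and the Stable and recovery stages section run to recovery or withdrawal. The score analysis uses baseline, "every treatment time and 1 month after palsy onset". The Primary outcome section speaks of a measurement one month after therapy.

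**The concern.** Both durations are times to an event. If the event has not happened when observation stops, the data show only that the time is longer than the time observed. One-way ANOVA and Kruskal-Wallis need a number for every patient, so the analyst has two choices.

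1. **Leave these patients out.** The comparison is then of speed among those who recovered. It selects on the outcome, ignores how many recovered, and departs from the promised intention-to-treat analysis. An arm with few recoveries can look nearly as fast as one with many.
2. **Enter the last observed day as the recovery day.** This records recoveries that did not occur. If one arm loses more patients early, its times look shorter for that reason alone.

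The Kruskal-Wallis fallback is triggered by the shape of the distribution and deals with neither problem. The method named in the protocol is therefore unsuitable for data that the protocol expects. This is more than a detail left for a later analysis plan.

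**Working it through.** **The plan's own figures.** The sample size rests on score changes. (1.96 + 1.28)² × (10² + 18²) / 13² = 26.34 and (1.96 + 1.28)² × (1² + 3²) / 2² = 26.24, so 27 per group. 27 × 1.2 = 32.4, so 33 per group and 132 in all. These reproduce. The article gives no power or sample size for the two durations, so there is no stated figure to test there.

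**Patients without a value, from the article alone.** 20% of 33 is 6.6 patients per arm lost to dropout. Those still unrecovered at the last assessment come on top. The article does not give their share.

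**How selecting on recovery shrinks a difference.** Assumptions: exponential recovery times, medians of 20 and 40 days, observation to day 30, no withdrawal. With rate λ = ln 2 / median and F = 30:

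- proportion recovered: p = 1 − exp(−λF)
- mean time among the recovered: 1/λ − F·exp(−λF)/p

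| Median | True mean 1/λ | exp(−λF) | p | Mean among recovered |
|---|---|---|---|---|
| 20 days | 28.9 | 0.354 | 0.65 | 28.9 − 30 × 0.354/0.646 = 12.4 |
| 40 days | 57.7 | 0.595 | 0.41 | 57.7 − 30 × 0.595/0.405 = 13.7 |

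A true gap of 57.7 − 28.9 = 28.8 days becomes 13.7 − 12.4 = 1.3 days. The difference of 65% v 41% recovered is not used.

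**Dependence on follow-up length.** Simulation of four arms of 33, exponential medians 20/27/27/40 days, 20% withdrawal, two-sided 0.05:

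| Follow-up | ANOVA, recovered only | Log-rank, all randomised |
|---|---|---|
| 30 days | 0.03 | 0.34 |
| 90 days | 0.20 | 0.56 |
| 180 days | 0.42 | 0.61 |
| open-ended | about equal | about equal |

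At 30 days the ANOVA rejects no more often than the nominal 0.05, so it has no useful power.

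**Dependence on recovery rate at 30 days.** Four arms of 33, visits every 2 days, 20% withdrawal, assumed recovery hazard ratios against group D of 2.0 (A), 1.5 (B) and 1.5 (C), 1,000 runs per scenario:

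| Group D recovered by day 30 | 30% | 50% | 70% | 90% |
|---|---|---|---|---|
| All patients with no recovery time | 63% | 42% | 24% | 10% |
| Log-rank | 0.28 | 0.40 | 0.51 | 0.59 |
| ANOVA, recovered only | 0.07 | 0.05 | 0.14 | 0.32 |
| Kruskal-Wallis, recovered only | 0.07 | 0.05 | 0.12 | 0.27 |
| ANOVA, last day as value | 0.16 | 0.29 | 0.45 | 0.54 |

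**False differences.** Equal recovery in all arms, withdrawal assumed at 40% in group D and 10% elsewhere, 2,000 runs. ANOVA on the last observed day rejects in 0.21, 0.12 and 0.09 of trials at 50%, 70% and 90% recovery, against a nominal 0.05. ANOVA on recovered patients stays at 0.05 to 0.07.

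**The case against.** The strongest reply is that the loss depends on a cut-off the article does not clearly set for recovery time. The one-month point is tied to MRI, electrophysiology and the repeated-measures score analysis, while the Abstract and the Stable and recovery stages section run to recovery or withdrawal. With follow-up to recovery, only withdrawals lack a value. A two-arm check (medians 20 and 40 days, 33 per arm, 20% withdrawal over days 0 to 30, open-ended otherwise) gave 71% for ANOVA on recovered patients and 73% for log-rank. Recovery times less spread than exponential also help: with a Weibull shape of 2 and a 90-day horizon, both tests have about 100%. This stands. It limits the size of the problem, but withdrawn patients still have no time to recovery, and Table 1 points to a short horizon.

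Three further points also stand:

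- The trial is sized on score changes, and these are analysed by repeated measures, where unrecovered patients still contribute their scores.
- Time to first change is probably less affected, since most patients may change score within a month. Withdrawal before any change still leaves it undefined.
- A reader might infer that ANOVA here always hides real differences. That describes only the analysis of recovered patients. With the last day entered, less power is lost (0.54 v 0.59 at 90% recovery) and the risk is a false difference instead. The article does not say which handling is meant.

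**Conclusion.** The point holds in this form: the test fixed for two durations under the primary outcome has no valid value for patients whom the article itself expects, and either way of supplying or omitting a value is unsound. The direction and size of the error are not fixed by the document. In the follow-up scenarios the power loss runs from almost all (0.03 v 0.34 at 30 days) to almost none (open-ended follow-up). These figures rest on assumed exponential times, assumed medians or hazard ratios, and 20% withdrawal unrelated to recovery. The false-positive figures rest on an assumed 40% v 10% withdrawal.

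A reader might conclude that the trial's main result is uninterpretable, or that the 30-day loss is what will happen. The document supports neither: the score analysis is untouched, and the horizon for recovery time is stated inconsistently. The change should be made, but it does not rank as a fault that invalidates the trial.

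**What to change.** In the Statistical analysis section, replace ANOVA and Kruskal-Wallis for both durations with Kaplan-Meier curves and a four-group log-rank test, or a Cox model with baseline score as covariate. Include all randomised patients and censor those without the event at their last scale assessment.

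Two definitions are needed first: the scale score that counts as complete recovery, and one follow-up horizon for this analysis. For the horizon, Table 1, the Stable and recovery stages section and the Statistical analysis section must be reconciled.

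Report also the proportion recovered at 1 month in each arm, with confidence intervals.

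The cost is a few more lines of analysis text. Onset date and visit scores are already collected, so no new data are needed. The replacement assumes that withdrawal is unrelated to recovery, which a sensitivity analysis should check.

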## Abstract

**Background:**

Although many patients with facial paralysis have obtained benefits or completely recovered after acupuncture or electroacupuncture therapy, it is still difficult to list intuitive evidence besides evaluation using neurological function scales and a few electrophysiologic data. Hence, the aim of this study is to use more intuitive and reliable detection techniques such as facial nerve magnetic resonance imaging (MRI), nerve electromyography, and F waves to observe changes in the anatomic morphology of facial nerves and nerve conduction before and after applying acupuncture or electroacupuncture, and to verify their effectiveness by combining neurological function scales.

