**Methods/Design:**

A total of 132 patients with Bell’s palsy (grades III and IV in the House-Brackmann [HB] Facial Nerve Grading System) will be randomly divided into electroacupuncture, manual acupuncture, non-acupuncture, and medicine control groups. All the patients will be given electroacupuncture treatment after the acute period, except for patients in the medicine control group. The acupuncture or electroacupuncture treatments will be performed every 2 days until the patients recover or withdraw from the study. The primary outcome is analysis based on facial nerve functional scales (HB scale and Sunnybrook facial grading system), and the secondary outcome is analysis based on MRI, nerve electromyography and F-wave detection. All the patients will undergo MRI within 3 days after Bell’s palsy onset for observation of the signal intensity and facial nerve swelling of the unaffected and affected sides. They will also undergo facial nerve electromyography and F-wave detection within 1 week after onset of Bell’s palsy. Nerve function will be evaluated using the HB scale and Sunnybrook facial grading system at each hospital visit for treatment until the end of the study. The MRI, nerve electromyography, and F-wave detection will be performed again at 1 month after the onset of Bell’s palsy.

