The purpose of this study is to investigate the effects of electroacupuncture therapy starting from the acute stage of Bell’s palsy. Symptom improvements will be evaluated by using the internationally accepted House-Brackmann (HB) Facial Nerve Grading System and the Sunnybrook facial grading system. Changes in facial nerve edema and nerve conduction will be analyzed by using MRI and neural electrophysiology techniques. The aim of the study is to provide a more reliable scientific basis for evaluating the effectiveness of electroacupuncture therapy for Bell’s palsy by combining clinical symptoms with physiology and electrophysiology findings.

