### Secondary outcomes

#### MRI examinations

The MRI examinations (MAGNETOM version 3.0T MRI Scanner using head matrix coils; Siemens Medical Solutions, Erlangen, Germany) will be performed within 7 days and at 1 month after the onset of Bell’s palsy. The conventional MRI protocol for this study consists of the following sequences. Three-dimensional constructive interference in the steady state will be performed in an axial orientation with the following parameters: 18-cm field of view (FOV), repetition time/echo time (TR/TE) of 8.58/3.91 ms, 64 sections of 0.5-mm thickness, with a matrix of 320×320 pixels, flip angle 50 degrees, bandwidth of 460 Hz, and acquisition time of 6 minutes, 12 seconds. A volume-interpolated body examination will be performed in precontrast and contrast T1 with the following parameters: 18-cm FOV, TR/TE of 20/3.69 ms, 32 sections of 1-mm thickness, with a matrix of 320×320 pixels, flip angle 12 degrees, bandwidth of 130 Hz, and acquisition time of 3 minutes, 4 seconds. Gadolinium-diethylenetriamine pentaacetic acid (contrast medium) will be administered intravenously at a dosage of 0.1 mmol/kg.

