#### Facial nerve electromyography

The surface recording electrodes will be placed on the orbicularis oculi muscle and the orbicularis oris. The reference electrode will be placed on the nasal bone. The ground electrode will be placed on one arm. Super strong stimulations will be applied to the stylomastoid foramen, and the latency and amplitude of the motor evoked potentials (M wave) at the initial location will be observed, first on the unaffected side and then at the same location on the affected side. The results of the two sides will be compared. Meanwhile, the R1/M-wave ratio in latency will be measured. The measurements will be performed within 7 days and at 1 month after palsy onset.

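### The only stated MRI test is a yes/no comparison of affected-side edema; it uses neither the graded measures nor the unaffected side and does not estimate the change in edema the trial sets out to study

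*Protocol article*

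**What the plan says.** The abstract's Background gives the aim as "to observe changes in the anatomic morphology of facial nerves and nerve conduction before and after applying acupuncture or electroacupuncture". The main Background section repeats it: "Changes in facial nerve edema and nerve conduction will be analyzed by using MRI and neural electrophysiology techniques".

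The abstract's Methods/Design says MRI is done for "observation of the signal intensity and facial nerve swelling of the unaffected and affected sides". The MRI examinations section says scans "will be performed within 7 days and at 1 month after the onset of Bell’s palsy"; the abstract puts the first scan within 3 days. M-wave latency and amplitude are recorded "first on the unaffected side and then at the same location on the affected side", also within 7 days and at 1 month, and that section adds: "The results of the two sides will be compared".

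The Statistical analysis section then states, for MRI, only that "a χ^2^ test will be used to compare the edema onset frequency of the facial nerve on the affected side". For the electrophysiology it states: "One-way ANOVA will be applied to identify differences in results of facial nerve electromyography and F-wave detection between groups", with Kruskal-Wallis for non-normal data. For the House-Brackmann and Sunnybrook scales, the same section specifies score changes, time and a group interaction.

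**The concern.** The trial is justified by the need for objective evidence beyond function scales. The Background also raises a safety question: whether electroacupuncture in the acute stage might aggravate nerve edema. Both call for a measure of how much edema each patient has and which way it moves.

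A presence/absence call on one nerve keeps little of that. A nerve that is half as swollen, or more swollen, still counts as edematous. The patient's own healthy nerve, which could take out between-person variation in signal and nerve size, does not enter the test. A real difference between groups, including a harmful one, could therefore be reported as no difference.

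**Working it through.** **Aim, data and test side by side (MRI)**

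| Item | Where stated | Content |
|---|---|---|
| Aim | Abstract Background; Background | Change in edema |
| Measures | Abstract Methods/Design | Signal intensity and swelling |
| Sides | Abstract Methods/Design | Unaffected and affected |
| Times | Abstract; MRI examinations | First scan (within 3 or 7 days) and 1 month |
| Test | Statistical analysis | χ² on edema frequency, affected side, no time named |

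The test row uses one side, no graded measure and no change. This mismatch rests on the text alone.

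**Sample size used for the illustration.** The plan gives no power figure for MRI. Its Sunnybrook calculation reproduces: (1.96 + 1.28)² × (10² + 18²) / 13² = 10.4976 × 424 / 169 = 26.34 (stated 26.33), rounded up to 27 evaluable per group.

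**Assumptions, none from the documents.** A normally distributed 1-month measure with SD 1; a true reduction of 0.7 SD; two arms of 27; two-sided 5%; edema called present above a fixed cut-off; edema in 50%, 80% or 90% of the comparison arm.

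**Continuous measure.** Noncentrality = 0.7 × √(27/2) = 2.57 on 52 degrees of freedom; power 0.71.

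**Yes/no call.** Treated-arm edema rate = Φ(z_q − 0.7), where q is the comparison-arm rate. Power of the uncorrected χ² test is by exact enumeration of the two binomials.

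| Comparison arm | Treated arm | Power |
|---|---|---|
| 50% | 24.2% | 0.505 |
| 80% | 55.6% | 0.502 |
| 90% | 72.0% | 0.423 |

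**Worsening by 0.7 SD.** The treated rate is Φ(z_q + 0.7): 93.8% from 80% and 97.6% from 90%. Power falls to 0.348 and 0.164, because few patients are left to move from no to yes. The continuous measure still gives 0.71.

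**Adjusting for the first measurement.** If that measurement is truly pre-treatment and correlates r with the 1-month value, the effective difference is 0.7/√(1 − r²):
- r = 0.5: 0.81, power 0.83.
- r = 0.7: 0.98, power 0.94.

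If treatment has already acted by the first measurement, adjustment removes part of the effect. With r = 0.7:
- Half of the effect already present: adjusted difference 0.7 − 0.7 × 0.35 = 0.455 SD; power about 0.63.
- All of it present: 0.7 − 0.7 × 0.7 = 0.21 SD; power about 0.19.

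Both are below the unadjusted 0.71.

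**Does the first measurement precede treatment?** Inclusion is within 2 days of onset. Groups A and B are treated every 2 days in the acute stage, and the common electroacupuncture of groups A–C starts on day 8. A first scan or recording at any time up to day 7 may therefore follow the start of treatment. No section rules this out.

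**The case against.** **The electrophysiology.** A reader might infer that the unaffected side and the first value are discarded there too, and that the ANOVAs are run on raw values. The documents do not support this. The electromyography section says the sides will be compared, and the ANOVA sentence speaks only of results, which could be side ratios or changes. The exact response variable is detail that an article may leave to a fuller document. This objection stands, and the point is confined to MRI as a defect; for the M wave there is only a suggestion of consistency.

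**The word onset.** A reader might also infer that the χ² test is empty because edema is settled before treatment begins. The documents give no source for when edema arises or resolves. Edema frequency at the 1-month scan could show complete resolution. What remains is insensitivity to partial change, and to worsening where edema is common.

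**Validity.** Comparing 1-month findings between randomized groups is valid without a baseline. The loss is in precision and in the match to the aim.

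**Baseline adjustment.** The objection that the first scan may not be a baseline is correct, and it rules out unconditional adjustment.

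**Feasibility and size.** The MRI section names no quantified measure, so a ratio needs extra reading of the images. The power figures rest on assumed values and on one pair of arms, whereas the plan describes tests across all four.

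None of this supplies the missing MRI analysis. The section chose a named binary test, so this is more than detail left out.

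**Conclusion.** The point holds for MRI. The stated test does not estimate the promised change in edema, and it leaves the graded measures and the healthy side out of the comparison. Under the assumptions above, a 0.7 SD reduction would be detected with power of about 0.71 on the continuous measure against about 0.42 to 0.51 on the yes/no call. These figures show direction and rough scale only; the documents supply no biomarker SD, correlation or edema rate. Further gain from adjustment is available only if the first value is truly pre-treatment, which the article does not establish.

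The outcome is secondary, but it carries much of the trial's stated rationale, so the change is worth making.

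**What to change.** In the Statistical analysis section:

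1. Replace the χ² test as the MRI comparison with a between-group analysis of the 1-month affected-to-unaffected signal-intensity ratio, and treat the nerve-swelling measure likewise.
2. Keep yes/no edema frequency as a descriptive table at each time.
3. Analyse 1-month M-wave amplitude and latency as an affected/unaffected ratio or difference, in line with the electromyography section.
4. Reconcile the first-MRI window (within 3 days in the abstract, within 7 days in the MRI section), and state for each first measurement whether it precedes the first study treatment.
5. Use the first measurement as an ANCOVA covariate only where it was taken before that treatment. Otherwise compare 1-month values without it.

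The cost is wording, one clarification of timing, and measuring both nerves on scans already planned. No extra visit, scan or patient is needed.
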